### 4.1. Sample Size

Calculation of sample size

No studies have reported on the influence of MT on the reduction in cervical fat in patients with sleep apnea and evaluations of obstruction patterns in DISE before and after. Our study will initially be a pilot study, with 15 patients in the control group, 15 patients in the moderate MT apnea group, and 15 patients with MT-CPAP severe apnea.

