### 4.2. Definition of Variables

The variables that we will measure in all patients and that are reflected in the data collection table using IBM SPSS Statistics version 28 with Windows software are as follows:Age;Sex;Weight;Height;BMI;Abdominal circumference (at the level of the navel);Neck circumference (with a flexible tape on the most prominent part; for this, it is necessary for the patient to be standing, with arms hanging at the sides, head erect, and gaze forward);Measurement with IOPI of tongue force and buccinator muscle;Measurement with digital spoon (DS);Initial AHI;Ranking of velum, oropharynx, tongue base, and epiglottis (VOTE) in DISE, before and after;Ultrasound measurements: echo intensity, tongue height (mm), and tongue width (mm).

To develop the protocol, patients with sleep apnea underwent submental cervical ultrasound and DISE before starting to use the AirwayGym app (www.airwaygym.app, accessed on 27 January 2024) and after 3 months of treatment.

The AirwayGym app is a portable fitness app (Figure 2) intended for patients rather than athletes, and therapists rather than coaches provide the instructions. The novelty of this app is that it is the first healthcare app on the market that allows patients to directly interact with a smartphone without the need for any other device. The app focuses on improving proprioceptive deficits in patients with sleep apnea. When used with the app, the smartphone provides acoustic feedback on the effectiveness of the MT exercises performed [27].

The AirwayGym app comprises daily tension and concentration exercises (i.e., isometric and isotonic exercises, respectively) that can be performed anywhere. It offers the additional advantage of providing prompt feedback to allow patients to see their progress and resolve problems with the help of a therapist. Before each exercise, an animated demonstration and video provide instructions for performing the exercise. After each exercise, patients receive visual, acoustic, and tactile feedback as a score on the success of their performance. A chat function is available via which patients can contact the therapist directly. This app complies with regulations 2002/58/EC and (EU) 2016/679 regarding data protection. It is priced at EUR 8.99. Additional information can be found on the AirwayGym website.

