The distribution of visits to the center will be as follows:Pulmonology visit: Patients will be diagnosed with OSA in a pulmonology laboratory via an initial sleep study, which includes the measurement of baseline AHI, the nocturnal desaturation index, and the lowest oxygen saturation levels during the night.Otorhinolaryngology visit: Patients will be assessed by the otorhinolaryngologist, who will evaluate the anatomy and functionality of the upper airways using DISE and measure tongue strength with the IOPI and TDS. The AirwayGym app is recommended for patients with oropharyngeal hypotonia.Ultrasound visit: A neck ultrasound will be performed to measure tongue thickness (mm), height (mm), volume (cm^3^), and distance between the lingual arteries (mm) before DISE and at the start of treatment modulation with the app (Figure 4 and Figure 5).Monthly telemedicine follow-up: During the 3-month study period, all patients in the three groups will be monitored for adherence and incidents related to the prescribed treatment with the AirwayGym app.Three-month follow-up: All variables evaluated during the initial visit will be measured again after three months. The ultrasound visit is an evaluation added to this previously published protocol (Tongue +) [36]. A submental ultrasound will be performed in the context of sleep apnea.

The Kolmogorov–Smirnov test will be used for the distribution of quantitative variables. The chi-square test or Fisher test will be used as necessary for the study of categorical variables. Student’s *t*-test or ANOVA (for two or more samples) will be used to study the differences between quantitative variables.

Non-parametric tests (Mann–Whitney or Kruskal–Wallis) will be used if the variables to be analyzed do not follow a normal distribution. The level of statistical significance will be set at *p* < 0.

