### 5.1. Preliminary Results

Additionally, submental ultrasound may be useful to evaluate the effectiveness of MT in sleep apnea. Studies have shown that myofunctional therapy can increase the size and strength of the genioglossus and geniohyoid muscles, which can improve upper airway function and reduce sleep apnea. Submental ultrasound can be used to measure these muscle changes and evaluate the effectiveness of therapy. With 10% of the patients included, there were significant differences (*p* < 0.05) in the initial volume (mm^3^) and lingual thickness (mm) between the control patients and the patients in the groups with moderate–severe sleep apnea. After 3 months of myofunctional therapy, we found a statistically significant improvement in the values of the functional examination with IOPI and the digital spoon and a reduction in lingual thickness (mm) of >15% in the patients studied.

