### 5.2. Discussion

The purpose of this protocol is to establish a diagnosis and treatment model for patients with severe apnea. With new technologies, we can carry out personalized and targeted treatment using cost-effective and safe tools for our patients.

There are no publications on the influence of myofunctional therapy on the reduction in cervical fat in patients with sleep apnea and evaluations of obstruction patterns in DISE before and after. Our study will initially be a pilot, with 15 patients in the control group, 15 patients in the TM moderate apnea group, and 15 patients with TM-CPAP severe apnea. Adult obstructive sleep apnea syndrome (OSAS) that begins very early in life has been attributed to the abnormal development of anatomical structures that support the upper airway (UAS). This abnormal development may be related to genetic, epigenetic, environmental interactions, or all factors. There is a continuous interaction between normal orofacial development and orofacial motor functions, with the involvement of the sensorimotor innervation of the orofacial region, particularly the tongue and mouth. Myofunctional therapy is a theoretically effective treatment in patients with moderate OSAHS and an adjuvant treatment to continuous positive airway pressure therapy, but more scientific evidence is needed to establish its effectiveness. The hypothesis of our work is to study the sensorimotor function of the tongue (apraxia, strength, and stereognosis) before and after oropharyngeal exercises performed with an application based on proprioceptive rehabilitation called Airway Gym^®^ and to see if, in patients with sleep respiratory disorders that present abnormalities in the sensorimotor function of the UAS, there is a significant improvement after myofunctional therapy. Determining the knowledge of the fatty and muscular components can be decisive in the choice of pharyngoplasty techniques, in multilevel surgery, and as a possible predictor of response or failure to MT since, currently, the influence that MT can have on reducing cervical fat is unknown.

Given that the aforementioned tools only measure strength, we consider the previous study of cervical fat using ultrasound and its response to TM relevant in the study of collapse patterns during DISE.

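### Change within the patient from baseline to 3 months is a stated question, but the tests named for non-normal and categorical data are independent-sample tests, and the form of the t-test is left open

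*Protocol article*

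**What the plan says.** Several places in the protocol article set up a comparison of each patient with himself or herself:

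- Section 2.2 gives every group an ultrasound measurement at the start and again at 3 months.
- Section 2.3 lists the influence of myofunctional therapy (MT) on cervical fat and ultrasound parameters as an objective.
- Section 4.2 lists a variable that is paired by definition: "Ranking of velum, oropharynx, tongue base, and epiglottis (VOTE) in DISE, before and after".
- The visit schedule in section 4.3 states: "All variables evaluated during the initial visit will be measured again after three months".
- The hypothesis in section 5.2 compares tongue function before and after the exercises and asks whether "there is a significant improvement after myofunctional therapy".

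The statistical paragraph at the end of section 4.3 names the tests. For categorical data: "The chi-square test or Fisher test will be used as necessary for the study of categorical variables". For quantitative data it names Student's t-test or ANOVA, for two or more samples, without saying whether the t-test is paired. The fallback is explicit: "Non-parametric tests (Mann–Whitney or Kruskal–Wallis) will be used if the variables to be analyzed do not follow a normal distribution". Change scores are not named as the variable to be analysed.

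On size, section 4.1 says: "Our study will initially be a pilot study, with 15 patients in the control group, 15 patients in the moderate MT apnea group". The MT-CPAP group also has 15.

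**The concern.** Mann–Whitney, Kruskal–Wallis, chi-square and Fisher all assume that every observation comes from a different subject. Fifteen patients measured twice give 15 pairs, not 30 independent readings. If such a test is applied to baseline against 3 months, it leaves the differences between patients in the error term, although pairing would remove them. With positive correlation the standard error of the change is then overstated, the true type I error falls below the nominal level, and a real change may be reported as not significant.

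The gap is firmest where the article names the tests without leaving room for a paired form: non-normal quantitative change (ultrasound, IOPI, digital spoon) and categorical before-after data such as VOTE. Groups of 15 have little precision to spare. If the form of the test is settled only at analysis, it can also be chosen after the data have been seen.

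**Working it through.** **Plan's own figure.** There is none to reproduce. Section 4.1 gives 15 per group without power, effect size, SD or correlation.

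**Inputs.**
- From the document: n = 15 in one group, measured twice (sections 2.2 and 4.1).
- Assumed: two-sided α = 0.05. The printed threshold is cut off in the text available, which is not counted as an error; the preliminary results in section 5.1 use p < 0.05.
- Assumed: mean change d of 0.5, 0.8 or 1.0 baseline SD, and within-patient correlation ρ from 0 to 0.8. The only effect in the article is a fall in lingual thickness of more than 15%, without an SD, so it cannot be turned into d.

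**Standard errors, in baseline SD units.**
- Treated as independent: √(2/15) = 0.365. With t(0.975; 28 df) = 2.048, the observed change must exceed about 2.048 × 0.365 = 0.75 SD, whatever ρ is.
- Paired: √(2(1−ρ)/15). At ρ = 0.5 this is 0.258 and the threshold, with t(0.975; 14 df) = 2.145, is 0.55 SD. At ρ = 0.8 it is 0.163 and the threshold is 0.35 SD.
- Ratio of standard errors: 1/√(1−ρ), that is 1.41 at ρ = 0.5 and 2.24 at ρ = 0.8.
- Break-even: the paired test has fewer degrees of freedom, so it gains only when 1−ρ < (2.048/2.145)² = 0.91, that is for ρ above roughly 0.1.

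**Power of the t-tests.** The paired figures come from the noncentral t with 14 df and noncentrality d√15/√(2(1−ρ)). For d = 0.5 and ρ = 0.5 this is 0.5 × 3.873/1 = 1.94, giving 44%. For ρ = 0.8 it is 0.5 × 3.873/0.632 = 3.06, giving 81%. The unpaired figures come from 40,000 simulated sets of 15 correlated normal pairs.

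| d | ρ | Unpaired t | Paired t | Relative loss |
|---|---|---|---|---|
| 0.5 | 0 | 27% | 25% | none |
| 0.5 | 0.3 | 23% | 33% | 30% |
| 0.5 | 0.5 | 20% | 44% | 54% |
| 0.5 | 0.7 | 16% | 64% | 76% |
| 0.5 | 0.8 | 13% | 81% | 84% |
| 0.8 | 0.5 | 59% | 82% | 28% |
| 0.8 | 0.8 | 63% | 99.5% | 37% |
| 1.0 | 0.5 | 83% | 95% | 13% |
| 1.0 | 0.8 | 90% | 100% | 10% |

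Between ρ = 0.5 and 0.8 at d = 1.0 the largest loss is at ρ = 0.6: 1 − 84.5/98.0 = 14%.

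**Rank tests (4,000 simulations), Mann–Whitney against Wilcoxon signed-rank.** At d = 0.5: 23% against 23% (ρ = 0), 16% against 41% (0.5), 13% against 61% (0.7), 11% against 79% (0.8). At d = 1.0: 77% against 93% (ρ = 0.5) and 86% against 100% (0.8). These simulations use normal data, so for the non-normal data that would trigger the rank tests they are a guide only.

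**Actual type I error of the unpaired t-test on pairs** (nominal 5%): 2.1% at ρ = 0.3, 0.7% at 0.5, 0.1% at 0.7.

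**VOTE.** No power was computed for categorical data. The point there is structural: a chi-square or Fisher table of time point by category would count each patient twice as if independent.

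**The case against.** The best defence is that section 4.3 never assigns these tests to before-after pairs. The study has three groups, and t-test, ANOVA, Mann–Whitney, Kruskal–Wallis, chi-square and Fisher are all valid for comparing groups at baseline, at 3 months or on change scores. That stands. The harm arises only if an analyst feeds paired readings into an independent-sample test.

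Other points also stand:

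- Student's t-test can be run paired, so for normally distributed data the loss is possible, not established.
- Section 5.1 is not purely within-patient. Its p < 0.05 result on volume and thickness compares groups at baseline, which suits the listed tests. Only the next sentence concerns 3-month change, and it does not name its test.
- Section 2.3 lists several objectives without naming a primary one, so change within the patient is one stated question among several.
- The error would be in the conservative direction, in a pilot with no power target.

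It can also be said that a short article leaves paired or unpaired form to a fuller document. That would answer silence. It does not fully answer a paragraph that names its non-parametric and categorical tests one by one, none of them paired, alongside a variable defined as before and after.

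A reader might infer that most of the study's power is lost, or that its confidence intervals will be too wide. The documents support neither. The loss depends on a correlation and an effect size that they do not give, and the plan specifies no intervals.

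**Conclusion.** The point holds in a limited form. Change from baseline to 3 months within the patient is a stated question, and the tests fixed for non-normal quantitative data and for categorical data are not suited to it. For normal data the plan is ambiguous rather than wrong.

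If an independent-sample test were used on the pairs, it would be conservative for correlations above roughly 0.1. At an assumed change of 0.5 SD, the relative loss of t-test power runs from none at correlation 0 to 84% at 0.8. At 1.0 SD it is only about 10–14% for correlations 0.5 to 0.8. All of this rests on assumed correlation, effect size and two-sided α = 0.05, with n = 15 from the protocol article. It is a should-fix: the inference is central enough to need a named test, but the size of the harm is not established and its direction is towards fewer false positives.

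**What to change.** Revise the statistical paragraph of section 4.3 to separate two kinds of comparison:

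- **Within a group, baseline to 3 months.** Use the paired t-test on the 3-month minus baseline difference, with normality judged on that difference, or otherwise the Wilcoxon signed-rank test. Use the signed-rank or sign test for VOTE as an ordinal rating, and exact McNemar for binary items.
- **Between groups.** Keep t-test or ANOVA, Mann–Whitney or Kruskal–Wallis, and chi-square or Fisher, and say that they may be applied to change scores.

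The cost is about two sentences. No new data, visits or patients are needed.

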Submental ultrasound is a non-invasive technique used to evaluate the size of the genioglossus and geniohyoid muscles, which are important in keeping the upper airway open during sleep. These muscles are located at the bottom of the jaw and are inserted into the tongue and larynx.

In the setting of OSA, submental ultrasound can be used to determine whether the size of these muscles is adequate to keep the upper airway open during sleep. If these muscles are small or weakened, there may be an increased risk of airway obstruction and sleep apnea [44]. Due to MT ameliorating OSA and sensorimotor deficit in selected patients, all clinical information obtained from the muscle pattern can be a useful tool for more accurate future therapeutic decisions [11,45].

We are interested in comparing the results obtained from the anthropometric characteristics of our patients with other populations to verify if there are significant differences between them [46,47].

Despite the strengths of this pilot study mentioned above, we note several limitations. First, the number of participants is small. The number of patients in the control group is low because we found significant differences in the therapy group early during this study. We therefore decided not to enroll more patients in the control group because of the difficulties experienced by patients with severe OSAHS not given appropriate therapy.

There is no blinding since it is a diagnostic protocol. Mood disorders are not analyzed since the exclusion criteria include patients with serious illnesses or those taking treatments that affect apnea.

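### The only planned significance level is printed as p < 0, which no p-value can meet and which disagrees with the p < 0.05 used in the preliminary results; it is most likely a truncated 0.05

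*Protocol article*

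**What the plan says.** Section 4.3 of the protocol article ends with two short paragraphs on analysis. They name a Kolmogorov–Smirnov check of distribution and chi-square or Fisher tests for categorical variables. For quantitative variables the text says "Student’s *t*-test or ANOVA (for two or more samples) will be used to study the differences between quantitative variables", and then "Non-parametric tests (Mann–Whitney or Kruskal–Wallis) will be used if the variables to be analyzed do not follow a normal distribution". The last sentence sets the criterion for all of these: "The level of statistical significance will be set at *p* < 0". A full stop follows and the section ends there.

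Section 5.1 (Preliminary Results) reports, on 10% of the patients, that "there were significant differences (*p* < 0.05) in the initial volume" and in lingual thickness between the controls and the groups with moderate–severe apnea. For the period after therapy it adds that "we found a statistically significant improvement in the values of the functional examination with IOPI and the digital spoon", with no threshold attached.

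Section 4.1 gives the group sizes: "Our study will initially be a pilot study, with 15 patients in the control group, 15 patients in the moderate MT apnea group", and a further 15 in the group with severe apnea who receive both therapies. It names no significance level.

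**The concern.** The sentence in section 4.3 is the criterion by which results from every listed test would be called significant. As printed it can never be satisfied, and the article's own preliminary results were judged by another value. A reader who wants to know the planned level has to infer it from a reported result, and a reported result does not set a plan. What is at stake is a clear, citable threshold for the remaining analyses. The design, the sample size and the choice of tests are not affected.

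**Working it through.** **1. Where a level could have been stated.**

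| Place in the article | Significance level given |
|---|---|
| 4.1 Sample Size | None; also no power, effect size or standard deviation |
| 4.3, last sentence | p < 0 |
| 5.1, baseline volume and thickness | p < 0.05 (a reported result) |
| 5.1, tongue strength measures (IOPI and digital spoon) after therapy | Called significant, no level |
| 5.2, limitations | Differences called significant, no level |

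Only section 4.3 sets a level for the plan. Only section 5.1 gives a usable number.

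**2. Can the printed rule be met?** A p-value lies between 0 and 1, so the probability that p < 0 is exactly 0 under any hypothesis. A simulation of 200,000 two-sample t-tests with 15 patients per group shows the same:

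| True difference | Share with p < 0 | Share with p < 0.05 (two-sided) |
|---|---|---|
| None | 0 | 0.0498 |
| 1 SD (assumed for illustration) | 0 | 0.752 |

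This shows that the printed value cannot be the intended one. It does not predict how the trial will be analysed, because nobody would apply the rule literally.

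**3. Does the rule agree with the rest of the article?** Under p < 0, neither statement of significance in section 5.1 could have been made. Under p < 0.05 the baseline statement is consistent with the plan. The two sections therefore conflict as printed, and they agree once 0.05 is restored.

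**4. Which value was meant?** Every conventional level begins with a zero and a decimal point, so the fragment alone does not identify the missing digits. The only level anywhere in the article is the 0.05 of section 5.1, which makes 0.05 the natural reading.

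**5. Is it a fault in the copy of the text?** Decimals are intact elsewhere: 0.05 in section 5.1, 29.9 in section 4.3 (upper limit of moderate disease) and 8.99 in section 4.2 (price of the app). A general loss of decimals is therefore unlikely, and nothing marks the sentence as redacted. Those three figures all stand inside a paragraph, however, whereas this one is the last text of its section. A cut at that exact point cannot be excluded without the published page.

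**6. Does anything else depend on the figure?** The planned total is 15 + 15 + 15 = 45, given as a pilot size with no power calculation. Changing the level from 0 to 0.05 alters none of these numbers.

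**The case against.** The strongest reply is that this is a misprint, or even a loss of characters at the end of a section, that any reader would silently correct to 0.05, so nothing follows from it. Much of this stands. The slip is evident, the intended value is recoverable from section 5.1, and no sample size depends on it. The uncertainty about the copy also stands, and it is why the published page should be checked first. What does not stand is that no correction is needed: the sentence is the plan's only statement of its decision threshold, and a value that must be inferred from a results paragraph has not been stated.

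It could also be said that a condensed article may leave such details to a fuller plan. That would answer silence on the level. It does not answer a level that is stated and stated wrongly. It does answer any complaint that the article fails to say whether tests are one- or two-sided. That detail may be left to the full protocol or analysis plan, and for ANOVA or Kruskal–Wallis the choice does not normally arise.

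A reader might go further and infer that the level was picked after data had been seen. The article does not show this; the 0.05 in section 5.1 is at least as consistent with 0.05 having been intended throughout.

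A reader might also tie the misprint to section 5.2, where the control group is said to be small "because we found significant differences in the therapy group early during this study". That passage names no threshold, and it gives a second reason, the difficulties of patients with severe disease who were not given appropriate therapy. Whatever one thinks of ending control enrolment in this way, the question would be the same had section 4.3 printed 0.05.

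**Conclusion.** The point holds as a minor error. The only planned significance level in the article is printed as p < 0, which is impossible to meet and inconsistent with the p < 0.05 applied in section 5.1. It is most likely a truncated 0.05. Its size is one figure, with no consequence for the group sizes, the tests or any other number.

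The conclusion rests on two assumptions: that the published article reads as the text at hand does, which is likely but not certain, and that the value used in section 5.1 is the one meant for the plan. It would be wrong to describe the trial as having zero type I error or zero power. That is the literal content of a misprint and not a property of the study.

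**What to change.** Check the last sentence of section 4.3 in the published article. If the digits are present there, nothing needs to be done. If it reads as quoted, correct the threshold to p < 0.05 so that it agrees with section 5.1, and issue this as a correction to the article. It would be helpful to add in the same line that tests are two-sided where a direction is possible; this is a suggestion, since the article does not say which was intended. The cost is one corrected figure and, if accepted, one added word. No sample size, procedure or other result needs to be changed.
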